## Abstract

**Background:**

Before the COVID-19 pandemic occurred in January 2020, the number of overseas visitors to Japan had increased threefold over the last decade. To minimize the risk of health problems, visitors should be able to access information on the health care systems of the places they visit. Most short-term overseas visitors are young adults. Although they are not very likely to get sick from noncommunicable diseases, they are at high risk for injury and often experience stomach ailments, fever, or nausea when travelling. The objective of this study is to evaluate culturally and linguistically appropriate health information on preventive health behaviours and the health care system in Japan. We will examine the level of satisfaction of overseas visitors to Japan with health care-related educational materials using a five-minute digital game named *Sa-Chan Japan.*

**Methods:**

Our study is a randomized controlled trial (RCT). We will assess both satisfaction and motivation before, during, and after the interventions and examine the changes over time. The intervention group will comprise overseas visitors who will view and answer questions in an animation named *Sa-Chan Japan*. The control group will comprise overseas visitors who will watch an English digital animation named *Mari Info Japan*. We will recruit 1002 participants through the *Macromill* Internet portal. We will contact overseas visitors who have either visited or wish to visit Japan from the United Kingdom, United States, and Australia. The participants will fill out a self-administered questionnaire online in the first quarter of 2021. We will determine the participants’ levels of satisfaction with the CSQ-8 (8-item Client Satisfaction Questionnaire). We will analyse the median score of the overseas visitors with both the Wilcoxon rank-sum and the Wilcoxon signed-rank tests. Our protocol of randomized controlled trials follows the SPIRIT guidelines.

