### Participants

#### Sample size

In this study, we expect to recruit 1002 participants via a Macromill internet panel. In the sample size calculation, a 95% confidence level and 80% power were used to detect a difference of 0.178 in the questionnaire score, with a standard deviation of 1.0, extra parameter of 0.0 and alpha of 0.05.

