### Outcomes

The primary outcome of this study is the difference in the average or median CSQ-8 (8-item Client Satisfaction Questionnaire) [29] score between the participants who will have played the *Sa-Chan* game and controls immediately after the interventions. We will assess the outcome using a self-administered questionnaire, the CSQ-8 scale, which has been used widely for health education [29] and has been shown to have reliable and valid in previous research [30]. The CSQ-8 is an eight-item questionnaire that uses a four-point Likert scale and will be used to assess the respondent’s level of satisfaction regarding the health care system and safety in Japan. The total score ranges from 8 to 32. A high score denotes greater satisfaction. The reliability of the questionnaire will be examined by Cronbach’s alpha.The second outcome of the study is the difference in motivation between the participants who will have played the *Sa-Chan* game and the controls immediately after the interventions. We will ask one question, “Are you likely to follow this information yourself”, and the participants will respond using a four-point Likert scale to determine whether they will change their behaviour or assess their level of motivation to follow the Japanese health-related guidelines. We will collect the data before and after the interventions. We will evaluate the data with the Information-Motivation-Behavioural Skills model [31]. This model has been used in a number of risk reduction behaviour studies [32].The third outcome is whether the participants understood the information presented in the *Sa-Chan* game. When a participant understands the information corresponding to each of 15 items, he or she will respond with “yes” to the item. The questions will be related to both interventions. If a participant understands how to deal with the following topics in Japan, he or she might choose correct answers.

In total, the questionnaire that will be used to assess the outcomes in (1), (2), and (3) and performing the intervention will take less than 10 min to complete. The participants will be visitors or individuals who wish to visit Japan.

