#### Data analysis

For the primary outcome of this study, we will analyse the difference in the median scores for the CSQ-8 recorded before and after the intervention between groups with the Wilcoxon signed-rank test. To compare the pre- and post-intervention scores between groups, the Wilcoxon rank-sum test will be used. We will adjust for other potential demographic factors that might affect the results of the multiple regressions.For the secondary outcome, regarding motivation, we will compare the differences in the pre- and postintervention scores for the behavioural change question between groups with the Wilcoxon rank-sum test.The third outcome is related to the participant’s understanding of the *Sa-Chan* game, which includes health knowledge questions. We will determine whether the answers are related to the characteristics of the participants.

All data analyses will be conducted using the JMP statistical package (version 14.0). The answers provided for the open-ended questions about Japanese health information will be examined by word-frequency analysis, with involves a word relationship network and co-occurrence, using the language analysis software Text Mining Studio (version 6.2) [33].

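### The abstract treats the rank-sum test as an analysis of the median CSQ-8, but the test does not target the median, the sample size rests on a mean difference, and the median is too coarse for the planned effect

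*Protocol article*

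**What the plan says.** Four places in the protocol article bear on this.

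- **Abstract, Methods:** "We will analyse the median score of the overseas visitors with both the Wilcoxon rank-sum and the Wilcoxon signed-rank tests". This is the only sentence that ties the median to the rank-sum test.
- **Outcomes:** "The primary outcome of this study is the difference in the average or median CSQ-8" score, compared between arms immediately after the interventions. No choice is made between the two measures, and no test is named. On the scale: "The total score ranges from 8 to 32".
- **Data analysis:** "To compare the pre- and post-intervention scores between groups, the Wilcoxon rank-sum test will be used". This sentence speaks of scores, not medians. The preceding sentence does name the median, but attaches it to the other test: "the difference in the median scores for the CSQ-8 recorded before and after the intervention between groups with the Wilcoxon signed-rank test".
- **Sample size:** "80% power were used to detect a difference of 0.178 in the questionnaire score, with a standard deviation of 1.0", with alpha 0.05 and 1002 participants.

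Nowhere does the article state that the two arms' score distributions are assumed to have the same shape and differ only in location.

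**The concern.** A primary analysis needs one effect measure, a test that addresses it, and a sample size built on it. Here the abstract points to the median, the between-group test is the rank-sum, and the sizing is on a mean difference.

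The rank-sum test compares the arms through the probability that a participant given the game scores higher than a control. It can be read as a test of medians if the arms differ by a pure shift. That assumption is unstated, and it is doubtful for a total score bounded at both ends, comparing a quiz game with a passive animation that may change the shape of the scores as well as their level.

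What is at stake is the reported primary result. A p-value from one quantity may be printed beside an estimate of another, and that estimate may be zero even when the intervention works exactly as planned.

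**Working it through.** **1. What the sample size is built on.** Inputs from the Sample size section: difference 0.178, SD 1.0, alpha 0.05, power 80%. Two-sided testing and 1:1 allocation are assumed, since neither is stated there.

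n per arm = 2 × (1.960 + 0.842)² × 1.0² / 0.178² = 2 × 7.849 / 0.03168 = 495.4, so 496 per arm and 992 in total. That is 1.0% below 1002. With 501 per arm the power is 80.4%. A one-sided test would give 782, which does not fit. The plan's figure is therefore consistent with a two-sample comparison of means, with the difference expressed in SD units.

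**2. What the rank-sum test responds to.** Simulation with 501 per arm, integer scores 8 to 32 and two-sided alpha 0.05. The control arm is normal with median 24 and SD 4. Shape, centre and SD are assumptions, because the article gives none. Both population medians are 24 in every row.

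| Game arm | Rank-sum rejects |
|---|---|
| Same distribution as control | 5.3% |
| Symmetric, SD 5, 6 or 8 | 5.7%, 5.3%, 6.2% |
| Upper half stretched to SD 5 | 17% |
| Upper half stretched to SD 6 | 40% |
| Lower/upper SD 3/5 or 5/3 | about 60% |

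The first row shows that the test holds its level when the distributions are the same. The second shows that equal distributions and P(game > control) = 0.5 are different conditions, and that the test reacts mainly to departures from the second. The remaining rows show that equal medians do not keep the rejection rate at 5%.

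**3. Whether the sample median can show the planned effect.** This step grants the pure shift. The planned effect in points is 0.178 × SD. With 501 per arm, an odd number, each arm's sample median is the middle score and so a whole number. The reported difference in medians can only be 0, 1, 2 and so on. Scores were simulated as a rounded normal at control centres from 23.6 to 24.4, with 1,500 trials per setting.

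| Assumed SD | Shift in points | Average share of significant trials with identical sample medians |
|---|---|---|
| 3 | 0.53 | about 40% |
| 4 | 0.71 | about 22% |
| 5 | 0.89 | about 12% |

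Power was about 77% to 80% throughout. Single settings ranged from about 3% to 77%, depending on where the centre falls relative to the rounding points. Monte Carlo error is small beside that range: with about 1,170 significant trials, the standard error at 77% is √(0.77 × 0.23 / 1170) = 1.2 points.

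Two settings at SD 4 show why the range is wide. At centre 23.6, rounding leaves both population medians at 24; 77.9% of trials are significant, and 32.1% are significant with identical sample medians, so 32.1 / 77.9 = 41%. At centre 24.0 the population medians are 24 and 25; the figures are 77.3% and 8.3%, so 8.3 / 77.3 = 11%. The true effect is the same in both.

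**The case against.** The other side has a good deal to say.

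- **The textual basis is narrow.** Only the abstract links the median to the rank-sum test. The Outcomes section names no test, and Data analysis puts the median with the signed-rank test. This stands. The point is one sentence plus an unresolved choice of measure, and the signed-rank wording is a separate matter.
- **The Outcomes section permits the average.** True, but this does not align the plan: the rank-sum test does not target a difference in averages either.
- **The rejections in step 2 are not errors about satisfaction.** A reader might infer from 17% to 60% rejection under equal medians that the trial has an inflated false-positive rate. The document does not support that. The plan never writes down an equal-medians null, and the arms in those scenarios differ in mean by about 0.3 to 0.8 points. In a rerun of the same four scenarios the rank-sum test rejected in 16%, 41%, 60% and 60%, and a Welch test of means in 22%, 60%, 84% and 86%. The differences are real, and a test of the mean finds them more often.
- **Misreporting is presumed.** No sentence says that a significant result will be read as a difference in medians, and reporting detail may sit in a fuller plan. That is fair, but the abstract does fix the median as the quantity that the test analyses.
- **A usable effect size could still emerge** from the planned multiple regressions. This is possible, although that sentence is loosely worded and does not make the regression estimate the primary effect.
- **The figures in step 3 depend on assumptions.** They do, which is why a range is given. The coarseness itself does not: a whole-number median cannot express a shift of 0.53 to 0.89 points.

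**Conclusion.** The point holds as a mismatch between effect, test and sizing quantity. The rank-sum test is not a test of medians without a shift assumption that the article does not make. Even with that assumption, the median is a poor carrier of a 0.178 SD effect on this scale: on average about 12% to 40% of significant trials would show identical medians, and about 3% to 77% in single settings. Those figures rest on assumed normal scores rounded to integers, SD 3 to 5, control centres 23.6 to 24.4 and 501 per arm.

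Type I error when the two materials produce the same score distribution is intact, and the sample size is not invalidated. The harm is confined to what is reported as the effect and how it is interpreted. It is worth correcting because it concerns the primary outcome and costs little.

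**What to change.** 1. **Outcomes:** replace the choice between average and median with one measure, the between-arm difference in mean post-intervention CSQ-8 total with a 95% CI. This matches the sample-size calculation.
2. **Abstract, Methods:** drop the description of the rank-sum test as an analysis of the median.
3. **If the rank-sum test is kept:** report an estimate that belongs to it with a 95% CI, either P(game > control) with ties counted as half, or the Hodges-Lehmann shift. On this scale the first is more informative. The Hodges-Lehmann estimate is the median of 501 × 501 = 251,001 whole-number differences, so it is itself a whole number and shares the coarseness shown above.
4. **Medians:** give them as description only, with no conclusion about them drawn from the rank-sum p-value.

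The cost is a few sentences and one estimate with its interval; no new data or participants are needed. Choosing the mean does settle the effect measure and is more than a change of wording, so it should be fixed before outcome data are seen. The small downside is that the headline result is no longer phrased as a median.

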**Discussion:**

Our research will utilize unique digital education strategies in a game that promotes health and safety among overseas visitors to Japan. We believe the results of this study will be useful in overcoming the current challenges regarding pretravel health requirements for overseas visitors worldwide.

**Trial registration:**

Version 1 of this trial was registered in the UMIN-CTR (University Hospital Medical Information Network Center Clinical Trials Registry), and the trial registration data are available on UMIN000042483, November 17, 2020.

## Background

The number of overseas visitors to Japan has steadily increased over the last decade [1] from 8.6 million in 2010 to 31.8 million in 2019 [2]. Notwithstanding the disruption to travel caused by the COVID-19 pandemic, this number will continue to rise due to increasing global tourism, international conferences, and major sporting events [2]. The potential for public health issues among mass gatherings at these large events should be considered [3].

It is imperative that overseas visitors are able to access information about the health care system of the country they are visiting to reduce risks and enjoy a comfortable stay [4]. Wadhwaniya and Hyder [4] examined how overseas visitors obtained information and where they visited. Some of these visitors were immunized at clinics before travelling to developing countries, even though the health risks were not confined to those countries.

There are three main concerns associated with the low level of health information accessed by overseas visitors to Japan. First, overseas visitors tend to be young adults and think they are not very likely to become sick while travelling, but they are at high risk for injury [5]. Only 18% (45 out of 241) of overseas visitors, with a median age of 30–39 years, accessed information about the Japanese health care system in our previous study [6]. As one of the fastest growing host countries, Japan needs to rethink how its health care information will reach overseas visitors, including young adults.

Second, the effectiveness of pretravel health issue prevention is dependent upon the presentation and content of the information [7, 8]. Health information for overseas visitors is usually provided through websites, pamphlets, travel books, or visiting clinics in their home countries [7, 9, 10]. Currently, public health authorities of various countries provide health and safety information. This information is located at disparate places and may be inadequate for certain overseas visitors. Furthermore, much of the information is about infectious diseases and immunizations for developing countries [11–13]. For instance, in our earlier study conducted before COVID-19, we concluded that overseas visitors are most concerned about medical costs, the Japanese language, and informed consent at clinics and hospitals, but there is not enough information to decrease these concerns [6, 14]. Third, although studies have confirmed that educational games are beneficial for sharing health-related information [15, 16], we have not found educational games that provide health-related information for travellers.

Overseas visitors generally consider Japan a developed nation that has a health care system with high standards. However, they do not know how to navigate the Japanese health care system should the need arise. Host nations have an obligation to provide accurate and useful information to overseas visitors about their health care system [17], illness prevention [18, 19] and procedures to access health facilities [14, 17, 20] in an efficient manner so that overseas visitors are not anxious about visiting other nations [4, 21]. Comprehensive and effective health education methods can convey vital information. Advancements in digital technology are driving changes, and information is now provided in several languages and in various formats [22]. These changes benefit most visitors, including young visitors, who are more likely to be at risk of injury when visiting foreign countries.

A digital game is an attractive way to distribute visually and culturally relevant information [23–25]. In a previous study, a digital game on insulin therapy for children with type 1 diabetes was used, and non-supervised usage of the educational game “L’Affaire Birman” was able to improve insulin titration and carbohydrate quantification results [26, 27]. Another game used by general surgery residents in classrooms showed a significant increase in short- and long-term medical knowledge that was retained, with high learner satisfaction [28]. A separate study on lecturing nursing students showed that an educational game was both liked and accepted by the students and considered a satisfying teaching technique [16].

Digital games can also be used to share information on travel health with overseas visitors. In this research, we will evaluate the effect of a five-minute digital game titled *Sa-Chan Japan* (Table 1). We will examine the levels of satisfaction and motivation of overseas visitors to Japan regarding their educational experience.

**Table 1 Tab1:**
[figure not shown]
Intervention group

*Sa-chan Game*: Contents of Japanese health & safety game for international visitors

## Methods

### Study design and procedures

We will conduct this randomized controlled trial to examine the efficacy of an animation game in improving both satisfaction and behavioural changes among current and potential visitors to Japan. The participants will complete the survey online. The participants will answer a questionnaire on the satisfaction and behavioural changes prior to and after participating in one of two interventions. We will evaluate the changes in their satisfaction and motivation levels (Fig. 1).

**Fig. 1 Fig1:**
[figure not shown]
Schematic design of study

### Participants

#### Sample size

In this study, we expect to recruit 1002 participants via a Macromill internet panel. In the sample size calculation, a 95% confidence level and 80% power were used to detect a difference of 0.178 in the questionnaire score, with a standard deviation of 1.0, extra parameter of 0.0 and alpha of 0.05.

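### The stated 80% power is not tied to one primary comparison: the sample-size inputs fit a comparison of means, the analysis names Wilcoxon tests, and the text does not say which score the SD of 1.0 describes

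*Protocol article*

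**What the plan says.** Three sections of the protocol article bear on the primary comparison.

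- **Sample size.** The target is given as "we expect to recruit 1002 participants via a Macromill internet panel". Its basis is that "80% power were used to detect a difference of 0.178 in the questionnaire score, with a standard deviation of 1.0", followed by "extra parameter of 0.0 and alpha of 0.05". No test is named, and nothing says whether the difference and SD belong to a post-intervention score or to a change.
- **Outcomes.** The primary outcome is "the difference in the average or median CSQ-8 (8-item Client Satisfaction Questionnaire") between game and control participants immediately after the interventions. That is a post-intervention comparison, with the summary measure left open between mean and median.
- **Data analysis.** The primary outcome is first assigned to a signed-rank test on before and after scores between groups. The next sentence reads "To compare the pre- and post-intervention scores between groups, the Wilcoxon rank-sum test will be used". Multiple regression is mentioned for adjustment, and the factors named there are demographic. Pre-intervention CSQ-8 is not named as a covariate.

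No pre/post correlation, score distribution or allocation ratio is given.

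**The concern.** A power statement is useful only for the variable and the test it was computed for. Here the sizing inputs are those of a comparison of means, the endpoint may be a mean or a median after the intervention, and the analysis is rank-based and brings in the pre-intervention score. A reader faced with a null result would want to know what difference the trial could have detected, and the text does not allow a single answer. Changing the type of test matters little. Changing the variable from a single score to a pre-to-post change can matter a great deal in either direction, because the SD of a change depends on the pre/post correlation.

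**Working it through.** **Inputs from the Sample size section:** N = 1002, difference δ = 0.178, SD σ = 1.0, α = 0.05, power 80%.

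**Assumptions not in the document:** 1:1 allocation (n = 501 per arm), two-sided test, normally distributed scores, and the pre/post correlation ρ, shown as a range.

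**1. Reproducing the plan's figure (two-sample comparison of means).**

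n per arm = 2(1.960 + 0.842)²(σ/δ)² = 2 × 7.849 / 0.178² ≈ 495.4, so 496 per arm and 992 in total (993 with the t distribution). The stated 1002 is within 1%.

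Power at 501 per arm: δ√(n/2)/σ = 0.178 × √250.5 = 2.817. Then Φ(2.817 − 1.960) = 80.4%. A one-sided test would need only 782 in total and does not fit.

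**2. Same inputs, rank-sum test.** Under a normal shift the rank-sum test has asymptotic efficiency 3/π = 0.955 relative to the t test. Effective n = 501 × 0.955 = 478.4, so 0.178 × √(478.4/2) = 2.753 and Φ(2.753 − 1.960) = 78.6%. Noether's formula gives 78.4% and a simulation of 20,000 replicates gives 78.2%. About 1040 participants would be needed for 80% (1038 by efficiency, 1044 by Noether), or the detectable difference becomes 0.181 instead of 0.178.

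**3. Rank-sum on change scores, if 1.0 is the SD of a single score.** With equal SDs before and after, SD of change = √(2(1 − ρ)).

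| ρ | SD of change | Rank-sum power |
|---|---|---|
| 0.3 | 1.183 | 64.3% |
| 0.4 | 1.095 | 71.0% |
| 0.5 | 1.000 | 78.6% |
| 0.6 | 0.894 | 86.8% |
| 0.7 | 0.775 | 94.5% |

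Power is 80% when the SD of change is 2.753/2.802 = 0.983, that is ρ = 1 − 0.983²/2 ≈ 0.52. At ρ = 0.50 the change-score power equals the single-score value in step 2.

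**4. Mean post-intervention score adjusted for the pre-intervention score (ANCOVA).**

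- If 1.0 is the single-score SD, the residual SD is √(1 − ρ²). Power at ρ = 0.3, 0.4, 0.5 and 0.7 is 84%, 87%, 90% and 98%.
- If 1.0 is the SD of the change, the single-score variance is 1/(2(1 − ρ)) and the residual variance is (1 − ρ²)/(2(1 − ρ)) = (1 + ρ)/2. Power at the same correlations is 94%, 92%, 90% and 86%.

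Neither residual SD can exceed 1.0, so power is never below the 80.4% of step 1.

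**The case against.** The strongest reply is that nothing in the sample-size arithmetic is wrong and that the firm part of the loss is trivial. That stands: 1002 reproduces, and moving to the rank-sum costs under 2 points, or 0.003 in detectable difference.

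Even the sign of that small loss is not fixed. The CSQ-8 total is a bounded 8 to 32 sum of four-point items. For a non-normal distribution the rank test may be more efficient than the t test, or less (at the lower bound of 0.864, power is about 74.5%).

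The change-score figures also need a premise the protocol does not supply. If 1.0 is the SD of whichever score is tested, or 0.178 is meant as a standardised effect, the correlation does not enter. Outcomes points to a post-intervention comparison, and the rank-sum sentence can be read as comparing arms at each time point. This too stands, and it is why step 3 is a range.

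It can be added that a mean-based analysis is not foreign to the plan, since Outcomes allows the average and Data analysis mentions regression, and that the signed-rank test is named first. The first part is fair, so it would be too strong to say that the 80% belongs to a test the trial will never run. The second does not help: a signed-rank test is a paired or one-sample procedure and cannot by itself compare two independent arms.

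A reader might infer that the trial is underpowered, at 64% or 71%. The documents do not support that. They give neither the correlation nor the meaning of the SD, and under the same premise power exceeds 80% once the correlation is above about 0.52.

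**Conclusion.** The point holds as an inconsistency, not as an arithmetic error or a demonstrated lack of power. Sample size, Outcomes and Data analysis do not describe one primary comparison, so the stated 80% cannot be attached to the planned test. With normal data and 1:1 allocation, the rank-sum test has about 78.5% power on the stated inputs, which is not material by itself. The potentially material part is conditional: with a single-score SD of 1.0 and a test on change, power lies between about 64% and 94% for correlations of 0.3 to 0.7. The same 1002 participants can therefore support quite different readings of a null result, depending on a choice the text leaves open. It should be corrected because the correction is cheap and, with the baseline-adjusted analysis, removes the uncertainty.

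**What to change.** Preferred: name as the primary analysis the between-group difference in mean post-intervention CSQ-8, adjusted for pre-intervention CSQ-8 by ANCOVA, with a 95% confidence interval. Keep the rank-sum test as a sensitivity analysis, and state in Sample size which score the SD of 1.0 describes. The existing calculation is then conservative under either meaning of the SD.

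Alternative: if the rank-sum stays primary, name the one score it is applied to and restate the power as about 78.5% (or the detectable difference as 0.181 SD) under normality. If that score is the change, also state the assumed pre/post correlation and the power it implies.

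The cost is one or two sentences in Sample size and Data analysis, with Outcomes aligned to the chosen summary measure. Pre-intervention CSQ-8 is already collected, so neither option changes recruitment or data collection, and no extra participants are needed. Under the alternative, the stated power becomes slightly less favourable if a single score is tested, and depends on the stated correlation if change is tested.
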